### Primary and secondary outcome measures

Our primary outcome measure is participants’ self-reported alcohol consumption over the previous four weeks consistent with NHMRC guidelines [4]. Our secondary dependent variable is participants’ self-reported number of binge drinking occasions over the previous four weeks. Both primary and secondary outcome measures will administered at baseline and at follow-up. Participants will be asked to recall and report the absolute number of standard drinks they had consumed and the number of occasions when they engaged in binge drinking, that is, exceeding more than 4 standard drinks on a single drinking occasion, per week over the previous four weeks [34,105]. The self-report measures are based on the time-line follow back technique which has been shown to provide precise estimates of alcohol drinking [106]. This measure uses a number of techniques to aid recall such as linking alcohol drinking with significant events. In addition, the FAST will be administered to students recruited to the study at baseline [103]. The measure comprises four items (e.g. “How often during the last year have you failed to do what was normally expected of you because of drinking?”) and has demonstrated adequate validity and reliability to assess the extent of heavy and dependent drinking. FAST scores will be used as a means to screen participants for heavy alcohol consumption that is indicative of alcohol dependency. Participants identified as heavy or dependent drinkers will be excluded from the study prior to engaging in the protocol. Participants identified as heavy or dependent drinkers by the FAST will be provided with a leaflet providing advice on how to seek professional help for their alcohol consumption.

### Measures of psychological mediator variables

In keeping with research examining the effects of the intervention components on behavior, we will include measures of key psychological variables that are likely to mediate the impact of the motivational and self-control intervention techniques on alcohol consumption. Mental simulations are likely to be mediated by social cognitive variables related to motivation. In keeping with previous research that has demonstrated significant effects of mental simulations on variables form the theory of planned behavior, we will measure participants’ intentions, attitudes, perceived behavioral control, and subjective norms toward alcohol consumption. Standardized measures of the theory of planned behavior constructs used in previous studies will be adopted [42,107]. Intentions will be assessed with three items (e.g. “I intend to keep my alcohol drinking to within safe limits on each individual occasion or session over the next four weeks”) rated on six-point Likert-type scales ranging from 1 (*extremely unlikely*) to 6 (*extremely likely*). Attitudes will be assessed using five semantic-differential items (e.g. *enjoyable-unenjoyable*, *important-unimportant*) on six-point scales in response to a common stem (“For me, keeping my alcohol drinking to within safe limits on each individual occasion or session over the next four weeks is…”). Perceived behavioral control will be measured using three items (e.g. “How confident are you that you can keep your alcohol drinking to within safe limits on each individual occasion or session over the next four weeks?”) on six-point Likert-type scales ranging from 1 (*no control at all*) to 6 (*complete control*). Subjective norms will be assessed using three items (e.g. “Most people I know would approve of me keeping my alcohol drinking to within safe limits on each individual occasion or session over the next four weeks.”) on six-point Likert-type scales ranging from 1 (*disagree*) to 6 (*agree*). We will also assess generalized motivation to reduce alcohol consumption based on measures identified in previous research [34,107,108]. The motivation measure will adopt three items (e.g. “How motivated are you to keep your alcohol drinking to within safe limits on each individual occasion or session over the next four weeks?”) with responses made on six-point Likert-type scales ranging from 1 (*not at all motivated*) to 6 (*extremely motivated*).

We also expect that the effect of self-control training on alcohol consumption will be mediated by perceptions of subjective self-control capacity. We will therefore include a modified self-report measure of self-control to reflect current self-control capacity. Specifically, we will adopt the state self-control capacity scale to measure participants current self-control reserve (Ciarocco, Twenge, Muraven, & Tice, 2011). The scale comprises 25-items (e.g., *“I feel discouraged”*) assessed on seven-point Likert-type scales ranging from 1 (*not true*) to 7 (*very true*). In addition, we will assess dispositional levels of self-control using Tangney et al.’s [73] self-control questionnaire. The short version of the scale will be used which comprises 13-items (e.g., *“I am lazy”*) assessed on five-point Likert scales ranging from 1 (*not true at all*) to 5 (*very true*). The trait scale will only be administered to participants in the introductory session and not at follow-up.

### Data analysis

The first part of the intervention will involve testing intervention compliance. We will evaluate participants’ compliance with the mental simulation manipulation by conducting a content analysis of participants’ scripts written during the course of the intervention. We will evaluate compliance with the self-control training by examining participants’ level of engagement with the Stroop tasks administered over the course of the four-week intervention period. The use of online delivery of the self-control training intervention will enable us to analyze the percentage compliance with the task (including feigned compliance, engaging in the task but providing meaningless responses) and any improvements in Stroop performance over the course of the intervention relative to baseline. This will also enable us to evaluate whether there were differences in compliance across the challenging and easy self-control tasks. Similar to previous studies [14,34,108,109], we will conduct a 2 (self-control training: challenging vs. easy) × 4 (test week: 1, 2, 3 or 4) mixed-model ANOVA with repeated measures on the second factor to test for changes in Stroop performance over the course of the intervention. We will use averaged weekly Stroop response latencies as the dependent variable and hypothesize statistically-significant differences of medium effect sizes across intervention groups with longer latencies for participants receiving the challenging Stroop task, but we expect a statistically-significant training condition by time interaction effect of medium size such that the differences diminish over the course of the intervention as participants receiving the challenging task improve their self-control while participants receiving the easy task exhibit little or no improvement.

Data on the primary dependent variable of alcohol consumption will be analysed using a 2 (mental simulation: mental simulation vs. no mental simulation) × 2 (self-control training: challenging vs. easy) factorial between-participants analysis of covariance (ANCOVA) with alcohol consumption at follow-up as the dependent variable and baseline alcohol consumption and trait self-control as covariates. The analysis permits the main and interactive effects of mental simulation and self-control training intervention components. We predict statistically-significant main effects of medium size of mental simulation and self-control training on alcohol consumption, but also expect a statistically-significant, medium-sized interaction effect such that participants receiving the mental simulation and challenging self-control training components will report significantly lower levels of alcohol consumption than participants receiving either of the intervention components alone and participants that received neither manipulation.

We will also conduct mediation analyses to evaluate the effectiveness of the intervention components on alcohol consumption. This will be conducted using moderated linear regression analyses with indirect effects reproduced using Preacher, Curran, and Bauer’s [110] asymptotic bootstrapped algorithms and the bias-corrected bootstrap confidence interval to assess the statistical significance of the effects [111]. Specifically, we will develop binary dummy-coded variables to represent the effects of the mental simulation (1 = received mental simulation, 0 = received irrelevant visualization strategy) and self-control training (1 = received challenging Stroop task, 0 = received easy Stroop task) interventions with an additional variable computed to represent the interaction of the two. The primary outcome variable, follow-up alcohol consumption, will be regressed on these coded variables in the first instance to ascertain direct effects. This will be followed by analyses including multiple mediators of the effects including residualized change scores for the baseline and follow-up measures of the theory of planned behavior variables (intentions, subjective norms, attitudes, perceived behavioral control) and motivation as mediators of the mental simulation intervention and residualized change scores in state perceived self-control between baseline and follow-up as a mediator of the effect of the self-control training intervention. The unstandardized effects and confidence intervals will be used as input for Preacher et al.’s [110] bootstrapped algorithm computational tool to compute the indirect effects. We predict statistically-significant, medium-sized multiple mediation of the effects of the mental simulation intervention on follow-up alcohol consumption by the theory of planned behavior and motivational change scores and significant mediation of the effect of self-control training on alcohol consumption by state self-control change scores. Trait self-control will be included in the analyses as a control variable.

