### Self-control training

We will use regular practice on an online version of the Stroop color-naming task which will be delivered on the participant’s smartphone as a means to train and improve self-control resource capacity. As a fall back, in case the participant does not have access to a smartphone or does not own a smartphone, we will give participants the opportunity to conduct their self-control training on their personal computer using their web browser. Participants will be randomly allocated to an intervention group that engages in practice on using a ‘challenging’ version of the Stroop task for the duration of the intervention while participants allocated to the comparison group will engage in regular practice on an ‘easy’ version of the task that is not proposed to have any substantive effect on training self-control. Participants will practice on the task twice per day for the four weeks duration of the intervention. The tasks are similar to those developed for use in a previous study [85]. The challenging version of the task requires participants to respond to a series of word items in which the word meaning and the color of the ink in which it is written are incongruent (e.g., the word “green” written in red ink). The easy version is modified such that the word meaning and ink colour are congruent. There are equal numbers of word items with four possible colors (“red”, “green”, “yellow”, and “blue”) presented in random order. Participants will be given instructions on how to perform the task on a smartphone or personal computer during the initial visit to the laboratory. Participants will be offered the opportunity to use a generic smartphone loaned to them by the experimental team, their own smartphone, or their personal computer to engage in the training tasks. Participants will be given ample opportunity to familiarize themselves with the task and to ask any questions. Participants will be informed that they will be prompted to engage in the task via a text message sent to their smartphone or an email to their regular email address containing a URL link. Upon clicking the URL link, participants will be directed to a website to complete the version of Stroop color-naming task corresponding to the condition to which they will be allocated. Participants will be presented with a series of 238 color-word items presented in seven 34-item blocks on their screen with each item presented for 2000 milliseconds (ms). Participants will use a response panel presented on the smartphone touchscreen or their computer keyboard to identify the colour in which the word is written rather than respond to the word meaning. Participants will have 800 ms to provide a response by choosing the colour-word response options. Response latencies for each item will be logged along with errors. If no response is given, the response will be logged as “unanswered” and the next colour-word item will be presented.

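### The Stroop training check rests on weekly latency alone, so faster careless responding could be read as improved self-control

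*Protocol article*

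**What the plan says.** All references are to Methods in the protocol article.

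- **Outcome** (Data analysis): "We will use averaged weekly Stroop response latencies as the dependent variable". Accuracy is not part of it.
- **Model** (Data analysis): a 2 × 4 "mixed-model ANOVA with repeated measures on the second factor to test for changes in Stroop performance over the course of the intervention".
- **Interpretation** (Data analysis): latencies are expected to be longer on the challenging task, with an interaction such that "the differences diminish over the course of the intervention as participants receiving the challenging task improve their self-control". The easy-task group is expected to change little or not at all.
- **Feigning** (Data analysis): percentage compliance will be analysed, "including feigned compliance, engaging in the task but providing meaningless responses", and compliance will be compared between the two task versions.
- **Data available** (Self-control training): "Response latencies for each item will be logged along with errors". Items without a response are recorded as unanswered. The response window is short: "Participants will have 800 ms to provide a response".
- **Load** (Self-control training): 238 items per session, and "Participants will practice on the task twice per day for the four weeks duration of the intervention".

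The article does not say which items or sessions enter the weekly average, or what happens to a participant with no session in a given week.

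**The concern.** Outcome, model and inference are all fixed in the text, and the outcome cannot carry the inference by itself. Latency falls when a person inhibits the word more efficiently. It also falls when a person stops reading and taps quickly. The plan foresees the second behaviour but treats it only under compliance, and no sentence brings that check, or the logged errors, into the reading of the latency result.

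The direction of the artefact matters. Tapping speed does not depend on whether word and ink agree, so tapping pulls both groups towards one common latency. A narrowing gap is the pattern the plan has named in advance as evidence of training. At stake is whether the check can separate a working training task from growing disengagement, in a trial whose stated purpose includes explaining mechanisms.

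A smaller matter concerns the model. A conventional repeated-measures ANOVA needs all four weekly means, so someone who stops during week 2 and has no session in weeks 3 and 4 would normally lose weeks 1 and 2 as well.

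**Working it through.** **1. The plan's own figure.** No number is given for the Stroop check. The only design figure is the total sample size, 120 to 144 (Participants). It reproduces: with f = d/2, four groups, a 3-df F test, alpha .05 and power .80, d = 0.56 gives 144 and d = 0.62 gives 118, or 120 in equal groups. It is used here only to set group size: 120/2 = 60 to 144/2 = 72 per training condition.

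**2. Equal tapping in both conditions.** Let C and E be the genuine latencies on the challenging and easy tasks, T the tapping latency, and s the share of tapped sessions. Observed mean = (1 − s) × genuine + s × T, so the gap = (1 − s)(C − E). Assumed values, none from the documents: C = 620, E = 540, T = 300 ms, no real improvement.

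| s | Challenging | Easy | Gap |
|---|---|---|---|
| 0 | 620 | 540 | 80 |
| 20% | 556 | 492 | 64 |
| 30% | 524 | 468 | 56 |

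**3. Unequal tapping.** Narrowing = sC(C − T) − sE(E − T). With a second assumed set (650, 550 and 300 ms, gap 100 ms):

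- 10% vs 5%: 35 − 12.5 = 22.5 ms
- 20% vs 10%: 70 − 25 = 45 ms
- 30% vs 10%: 105 − 25 = 80 ms
- 10% vs 20%: 35 − 50 = −15 ms, so the gap widens

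The sign changes when feigning on the easy task exceeds 350/250 = 1.4 times that on the challenging task (320/240 = 1.33 for the first set).

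**4. Would the interaction test react?** This was simulated with 1,500 runs per setting, the first set of latencies, no true improvement, and a tapping share rising linearly from 0 in week 1. Further assumptions are a between-person SD of 60 ms, a residual SD of 20 ms, and tapped sessions drawn independently from 14 per week. Rejection rates at nominal 5%:

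| Week-4 share | Both conditions (60 / 72 per condition) | Challenging only (60 / 72) |
|---|---|---|
| 0 | 4.9% / 4.4% | 5.9% / 5.4% |
| 5% | 7.3% / 9.1% | 70% / 78% |
| 10% | 17% / 18% | over 99% |
| 20% | 40% / 47% | 100% |
| 30% | 66% / 76% | 100% |

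The simulation spreads tapping evenly over participants. If a few people do most of it, within-person variance is larger and rejection is less frequent.

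**5. Do the logged errors help?** With four colours, guessing is right 25% of the time. If genuine accuracy is 92% (assumed), accuracy at s = 20% is 0.8 × 0.92 + 0.2 × 0.25 = 78.6%, and at 30% it is 71.9%. Falling accuracy therefore exposes tapping. Among correct items pooled over the week, the tapped share is 0.05/0.786 = 6.4% and 0.075/0.719 = 10.4%. The gap becomes 80 × 0.936 = 74.9 ms and 80 × 0.896 = 71.7 ms, against 64 and 56 ms. Restricting to correct responses removes about two thirds of the artefact, but not all of it.

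**6. Empty weeks.** Two sessions a day give 14 a week and 56 in four weeks. A week is empty only if all 14 are missed. If each week is empty with probability p, independently, the share lost under complete-case analysis is 1 − (1 − p)^4: 8%, 19%, 34% or 59% for p = 2%, 5%, 10% or 20%. If the same people account for every empty week, the loss is only p.

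**The case against.** The case on the other side is substantial.

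- **Silence on details.** A reader might infer that every logged session enters the average and that anyone missing a week is dropped. The article states neither. Item cleaning and missing weeks are commonly left to an analysis plan, which is not shown. This stands, so the point is limited to what the text does fix: latency as sole outcome and narrowing as improvement.
- **The compliance analysis.** Compliance, including feigning, will be examined and compared between tasks, so disengagement would be partly visible beside the latency result. This stands as partial protection. However, no rule says how that finding should alter the reading of the interaction.
- **Assumed magnitude.** All latencies and tapping rates are assumptions, only fast tapping shortens latency, and the sign can flip. This stands. Equal tapping also lowers easy-task latencies (540 to 492 ms at 20%), which departs from the predicted flat easy group and might be noticed. Tapping confined to the challenging task would match the prediction fully.
- **Other evidence.** The plan also looks at Stroop improvement relative to baseline, and the mechanism itself is tested with the self-report state self-control scale. Calling this interaction the only evidence on self-control would be too strong.
- **A simple accuracy filter is not neutral.** One might exclude sessions with 75 or fewer of 238 correct, the 99th percentile of guessing (mean 238 × 0.25 = 59.5). Reading the word is correct on congruent items and wrong on incongruent ones, so such a cut-off could remove genuine weak performers from the challenging group only. It would also miss half-tapped sessions: 119 + 119 × 0.25 ≈ 149 correct. This stands and shapes the fix.

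**Conclusion.** The concern holds in a limited form. The check makes weekly latency its sole outcome, reads a narrowing gap as improved self-control, foresees meaningless responding, and does not connect the feigning check or the logged errors to that reading. Faster careless responding could therefore pass for a training gain.

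The mechanism needs no difference in feigning between conditions: an equal, rising share shrinks the gap by the factor (1 − s). The size in this trial is unknown. Under the assumptions shown, the effect ranges from trivial (5% tapping in both conditions) to enough to make the interaction test significant in most runs. It reverses if feigning is commoner on the easy task by a factor above roughly 1.3 to 1.4.

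The loss from empty weeks is secondary. It follows from how a conventional repeated-measures ANOVA normally works, not from a stated rule, and depends on how many participants have a week with no session at all.

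A reader might go further and conclude that the drinking result is compromised. The documents do not support that: neither the primary ANCOVA nor the mediation models use Stroop latency. This is a cheap improvement to a manipulation check.

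**What to change.** Change the wording of the Stroop paragraph in Data analysis as follows.

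1. Compute weekly latency from correct responses, pooled over the items of the week. An average of session means would leave a tapped session with full weight.
2. Analyse accuracy and the unanswered rate by training × week beside latency. Read a narrowing gap as improvement only if accuracy does not fall.
3. Replace the repeated-measures ANOVA with a likelihood-based linear mixed model of training × week on all available weeks, so that people who stop contribute the weeks they completed.
4. Exclude sessions flagged as feigned only in a sensitivity analysis, with numbers excluded by training condition, because a single accuracy cut-off works differently on congruent and incongruent items.

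The cost is slightly more analysis and fewer items in each latency mean. No new data are needed, since latencies, errors and unanswered items are already logged.

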
The Stroop task is expected to approximately 5 minutes. Participants will complete the task to which they have been assigned immediately after the mental simulation task in the initial session and then repeat the Stroop task twice per day when prompted, at 7 am and 5 pm, throughout the four-week intervention period. All participants’ Stroop data will be uploaded to, and stored on, a remote computer server for subsequent retrieval to compliance analysis.

Participants will be reminded to practice the Stroop task once per week via emails and/or text messages throughout the four-week intervention period. After four weeks participants will be sent a series of reminder emails to prompt them to complete follow-up dependent measures of self-reported alcohol consumption and follow-up measures of psychological mediator variables, identical to those administered at baseline. Thereafter, participants will receive a full debrief and provided with an opportunity to receive the final group-level results of the intervention.

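### Each arm does only its own Stroop version, so converging weekly latencies can reflect practice on the harder task and do not show that self-control improved

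*Protocol article*

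**What the plan says.** **Versions.** Under Self-control training, the challenging version shows words whose meaning conflicts with their ink colour. Of the other version the article says: "The easy version is modified such that the word meaning and ink colour are congruent". Each prompt leads the participant to "complete the version of Stroop color-naming task corresponding to the condition to which they will be allocated".

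**Timing.** The first exposure is also arm-specific: "Participants will complete the task to which they have been assigned immediately after the mental simulation task in the initial session". Participants then "repeat the Stroop task twice per day when prompted, at 7 am and 5 pm, throughout the four-week intervention period".

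**Follow-up.** After four weeks participants are asked to "complete follow-up dependent measures of self-reported alcohol consumption and follow-up measures of psychological mediator variables, identical to those administered at baseline". No Stroop or other performance task common to both arms is described at any time.

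**Analysis.** The Data analysis section opens with compliance and then sets out the 2 × 4 mixed ANOVA: "We will use averaged weekly Stroop response latencies as the dependent variable". It predicts longer latencies in the challenging arm and a medium-sized training-by-week interaction in which "the differences diminish over the course of the intervention as participants receiving the challenging task improve their self-control", with little or no change in the easy arm.

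**The concern.** Item type and arm coincide completely. No participant supplies both congruent and incongruent latencies, so a within-person interference score (incongruent minus congruent), the usual index of inhibition, cannot be formed for anyone. Adjusting for the initial Stroop does not help, because that session also uses the assigned version.

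The predicted pattern is a slower start in the challenging arm, a gap that shrinks, and a nearly flat easy arm. That is also what a harder task with more room for speeding up would produce as people get used to the items and the response panel. The article nevertheless attributes the shrinking gap to better self-control and names no other explanation.

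At stake is the only performance-based evidence that the training did what the strength model says it does. A significant interaction could be reported as a successful manipulation of self-control when it shows only familiarity with the task.

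**Working it through.** **1. What each arm sees**

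| Time | Challenging arm | Easy arm |
|---|---|---|
| Initial session | incongruent | congruent |
| Twice daily, weeks 1–4 | incongruent | congruent |
| Follow-up | self-report only | self-report only |

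In each week the group contrast is (incongruent latency, challenging arm) − (congruent latency, easy arm). Its change over weeks is a change in self-control plus a difference in practice gain between two tasks. The design gives no second equation to separate the two terms. This step needs no numbers and is the basis of the point.

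**2. The plan's sample size**

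This is used only to set N. Inputs from the Participants section: d = 0.56 and d = 0.62, power 0.80, alpha 0.05. With f = d/2 (0.28 and 0.31), four groups, numerator df = 3 and rounding up to a multiple of 4, the noncentral F gives 144 and 120. This matches the stated range of 120 to 144, or 60 to 72 per Stroop arm.

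**3. How often practice alone gives a significant interaction**

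The documents state no latency SD, correlation or practice gain. All of the following are assumptions:
- weekly-mean SD 80 ms;
- between-week correlation ρ of 0.6, 0.8 or 0.9;
- change in self-control zero;
- easy arm flat, as the plan predicts;
- an extra practice gain g in the challenging arm, phased in over weeks 1 to 4 as 0, 0.5, 0.8 and 1.

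Simulated probability of p < 0.05 for the 2 × 4 interaction (2,000 runs per setting):

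| g (ms) | N = 120, ρ = 0.6 / 0.8 / 0.9 | N = 144, ρ = 0.6 / 0.8 / 0.9 |
|---|---|---|
| 0 | 0.05 / 0.06 / 0.05 | 0.05 / 0.04 / 0.05 |
| 10 | 0.08 / 0.14 / 0.24 | 0.09 / 0.15 / 0.28 |
| 20 | 0.25 / 0.46 / 0.79 | 0.30 / 0.55 / 0.86 |
| 30 | 0.50 / 0.84 / 0.99 | 0.61 / 0.91 / 1.00 |
| 40 | 0.79 / 0.98 / 1.00 | 0.86 / 0.99 / 1.00 |

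Adding 15 ms of general practice to both arms (ρ = 0.8) changes little: at N = 120 and g = 20 the rate is 0.48 instead of 0.46.

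**4. Closed-form check of one row**

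The interaction noncentrality is λ = N(g/2)²S / [80²(1 − ρ)]. Here S is the sum of squared deviations of the profile from its mean of 0.575: 0.330625 + 0.005625 + 0.050625 + 0.180625 = 0.5675. For N = 120 and g = 20 the numerator is 120 × 100 × 0.5675 = 6,810. The denominators are 2,560, 1,280 and 640, so λ = 2.66, 5.32 and 10.64. With 3 and 354 df the power is 0.24, 0.46 and 0.78, in agreement with the simulation.

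**5. Scale of the optional probe**

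Sessions: 1 + 2 × 28 = 57. Items: 57 × 238 = 13,566. Two switched blocks: 2 × 34 = 68, and 68/13,566 = 0.5%.

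**The case against.** The strongest reply is that this ANOVA is a compliance check and nothing depends on it. The article introduces it under compliance, and neither the primary ANCOVA nor the mediation model uses Stroop latency. The hypothesised mediator of the training effect is perceived self-control capacity, measured by a 25-item state scale given to both arms at baseline and follow-up. All of this stands, and it limits the point. But the text goes beyond compliance: it states a hypothesis, an effect size and a reading in terms of self-control, and that reading is what fails.

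A reader might infer that no drinking result could be tied to the self-control mechanism. The documents do not support that. The state scale is a common measure, free of the item-type confound, and mediation through it is planned. It is self-report, so what is missing is performance-based corroboration.

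A reader might also reach for a higher false-positive rate by assuming the same proportional practice in both arms. For example, a 10% speed-up from 600 and 400 ms gives gains of 60 and 40 ms, a 20 ms difference. With a change SD of 40 ms, a two-sample t-test on change is significant in 78% to 85% of trials. That is not the planned 2 × 4 test, and a 40 ms gain in the easy arm contradicts the predicted little or no improvement, so half of the expected pattern would visibly fail. The figures above use the planned test and keep the easy arm flat.

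The predicted group main effect is not a fault either. It confirms that the harder task is harder, and the article does not present it as a gain in self-control.

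**Conclusion.** The point holds as a limit on interpretation. The confounding of item type with arm follows from the design text alone. Given that, convergence of weekly latencies cannot be attributed to improved self-control, and the trial has no performance-based evidence of such a change.

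How often the check would mislead depends on assumed values: about 25% to 79% of trials for a 20 ms extra practice gain at N = 120, 30% to 86% at N = 144, and close to the nominal 5% if there is no extra gain. These figures illustrate the risk and do not estimate it.

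The primary analysis of alcohol consumption and the mediation test through the state scale are untouched. The latency data remain useful for describing engagement and practice.

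**What to change.** **Needed, at no cost.** In the Data analysis section, describe the 2 × 4 ANOVA as a check of engagement, task difficulty and practice. Remove the clause that attributes the shrinking gap to improved self-control. State that the between-arm test of self-control change rests on the self-reported state self-control scale.

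**Optional, at small cost.** In the first and last sessions, replace one of the seven 34-item blocks with the opposite version, so that every participant yields an interference score at start and end, and compare its change between arms. This takes 68 of about 13,566 scheduled items (0.5%), a change to the task script and no added session time. Report it as supportive only. It removes the item-type confound, but four weeks of practice on incongruent items still favours the challenging arm. In addition, the last session is remote and may be missed by poor compliers, and a sudden switch of version may itself slow responses. A different inhibition task given to everyone before and after training would separate self-control from practice on the trained items, at the price of an extra assessment.
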